#### Participant screening and informed consent

As the intervention is an educational package designed to be delivered by religious leaders to all attending members of a mosque, women’s circle or Qur’an class, agreement for delivering the intervention will be sought, for example, from the mosque committee chair and/or religious leaders and not from individual participants. We think this approach is proportionate given the very low risk associated with participation and the likely potential benefits of the intervention. However, we will seek written informed consent from all participants in the household for all other research activities.

Eligible households will fall into two possible categories:

1. Households with at least one child and one adult smoker: In this case, consent will be sought from an adult resident (ideally a non-smoker) for completing the baseline (and follow-up when requested) questionnaire. A non-smoking resident (ideally a child) will be asked to consent to provide a baseline (and follow-up when requested) saliva sample. Consent will be sought from the parents/carers for a child of less than 16 years old. Children will be provided with an age appropriate information sheet and no samples will be taken if they are unwilling to participate.

2. Households with adult residents only and at least one non-smoking adult living with a smoker: Consent will be sought from the non-smoking adult resident (ideally) for completing the baseline (and follow-up when requested) questionnaire and providing a baseline (and follow-up when requested) saliva sample.

The recruitment officer will go through the respective information sheet with the potential participant during their appointment and seek consent(s) as appropriate.

We are not offering any personal incentive to the participant for taking part in the study; however, participants will be told that if they agree to participate, a sum of £5 will go towards a charity of their choice from a pre-selected list. All consents will be obtained prior to registration of participants and before any trial specific baseline assessments.

### Sample size

#### Quantitative

As this is a pilot trial whose findings will inform sample size considerations for a definitive trial, no formal sample size calculations have been undertaken. However, with the number of clusters we seek to enroll we should be able to estimate recruitment and attrition rates, effect size and ICC.

In the case of the primary outcome, the pilot trial will also provide possible effect size and standard deviation (SD) values. If these values are similar to other studies
[11,38,39], we expect that the difference in the cotinine levels between people who have different levels of exposure according to the smoking restrictions at home will be more than 0.20 ng/mL. Using this, we will then plan to power the main trial to detect at least a 28% reduction in exposure to SHS. Based on an assumed standard deviation of 1.38, the estimated detectable difference of 0.20 in the mean cotinine levels between the two arms is expected. However, these assumptions are based on a different population and our study will help in testing these.

The sample size of a cluster trial depends on the number of clusters, cluster size and variation. Therefore, this study aims to determine the ICC and rates of recruitment and attrition in order to compute the design effect by which we would need to inflate the sample size if we were undertaking a fully powered individually randomised trial. We plan to recruit 14 mosques with sufficient variation to estimate ICC with some precision. Assuming that at least 50 households agree to participate from each mosque, we expect at least 20 households with a positive cotinine test as baseline. This investigation will also answer whether this is achievable. It is expected that the attrition rate will be no more than 20% for the post intervention assessment. However, actual attrition rates will aid in making adjustment to the sample size. In addition to this, these assumptions will also be tested for other outcomes.

### Outcomes

#### Pilot trial outcomes

Number of clusters (Islamic religious settings) and the size of each cluster (participants) for the main trial:

1. Recruitment and attrition rates for clusters and participants.

2. Successful recruitment strategies and barriers to recruitment.

3. Length of time required to reach participant recruitment saturation for each cluster.

4. Descriptive data on characteristics of participating clusters and participants.

5. Reasons for ineligibility of clusters and participants.

6. Reasons for willingness of clusters to be randomised.

7. Reasons for non-participation/non-consent of clusters and participants.

8. Estimate of the effect size of the primary outcome (salivary cotinine).

9. Calculation of the ICC for the primary outcome in order to inform the sample size required for a main trial.

10. Estimate of contamination between clusters.

Feasibility and resource requirements to deliver the intervention and assess its outcomes:

1. The costs associated with delivering ‘SFH’ through Islamic religious settings.

2. The feasibility and acceptability of measuring the primary outcome (salivary cotinine) including the response rate to obtaining saliva samples, and the extent and type of missing data with reasons.

3. The response rate for the household survey (including health care utilisation questions), including the extent and type of missing data with reasons.

SFH in Islamic religious settings

1. The facilitators and barriers for integration of ‘SFH’ into Islamic religious settings practice and how the facilitators might be enhanced / barriers be addressed.

2. The views and experiences of faith leaders and participants regarding the intervention.

3. People’s (that is, men’s, women’s and children’s) views and attitudes on the appropriateness of religious leaders taking on a health promotion role.

#### Definitive trial primary outcome

The primary outcome measure in a definitive trial would be salivary cotinine levels in non-smokers in the households at follow up.

#### Definitive trial secondary outcomes

Secondary outcomes in a definitive trial would be:

1. Smoking restrictions at home: We will assess the level of smoking restrictions at home through a questionnaire directed at the adults in the households.

2. Smoking status of adults and their intention to quit: We will assess the smoking status of the adults living in participating households.

3. Family health service use: We will ask about the health service use of members of the household in the three months before the intervention and in the three months during the intervention.

4. In addition, we will measure a number of other variables, which will be built into our enquiry tools for assessing the above outcomes. These will include family structure and composition (for example, number of adults and children, their age, gender, and ethnicity), socioeconomic status, employment status, number of rooms in the house and neighbourhood variables (for example, availability of smoke free environments, rural, urban, cigarette shops and so on). In addition, we will also ask about the frequency and mode of contact with the mosque, that is, prayers, study circles, Qur’an classes.

### Data Collection

#### Quantitative

##### Cluster baseline data

For each cluster in the study the following information will be recorded at the start of the study:

1. Type of cluster (ethnic and religious denominations).

2. Average estimates of people who attend two or more daily prayers.

3. Average estimate size of Friday congregation.

4. Average estimate size of study circle (men).

5. Average estimate size of study circle (women).

6. Average estimate size of Qur’an class (children).

7. Average age (self-reported by teacher) of students/children taught.

##### Survey

Approximately 50 households per cluster will be recruited for the trial. After determining household eligibility and seeking informed consent, recruitment officers will carry out a baseline household survey. This survey encompasses four main dimensions: (1) basic information about household adults and their health service usage; (2) basic information about household children and their health service usage; (3) household smoking behaviours and practices; and (4) information about the frequency and mode of contact with participating Islamic religious settings.

A follow up survey covering the same dimensions will be conducted at approximately three months post intervention start, in a selection of households who remain in the trial (a random sample of 90% of the families who test positive for exposure to SHS at baseline and a random sample of 10% of the families who test negative for exposure to SHS at baseline) in both arms of the trial.

##### Saliva

From each of the households recruited, the recruitment officers will also collect a saliva sample to measure salivary cotinine levels at baseline from a child in the house or, in the absence of a child, from a non-smoking adult member of the household. A second saliva sample will be collected from the same individual approximately three months post intervention start, in a selection of households who remain in the trial (a random sample of 90% of the families who test positive for exposure to SHS at baseline and a random sample of 10% of the families who test negative for exposure to SHS at baseline) in both arms of the trial.

Cotinine is a metabolite of nicotine that can be measured in three main forms: serum, saliva and urine. Out of the three, salivary cotinine is the most sensitive and specific measure of exposure to tobacco, with a half-life of 12 to 18 hours
[40,41]. It is measured by collecting saliva in the mouth and blowing it into a plastic container through a straw or by using a swab. The samples are subsequently analysed and a gas–liquid chromatography technique can detect cotinine levels as low as 0.1 ng/ml. Based on cotinine measurements taken as part of the Health Survey for England for the years 1996 to 2004, various thresholds for active and passive smoking have been defined for different age groups
[42].

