**Methods/Design:**

This is a pilot cluster randomised controlled trial of ‘Smoke Free Homes’, with an embedded preliminary health economic evaluation and a qualitative analysis. The trial will be carried out in around 14 Islamic religious settings. Equal randomisation will be employed to allocate each cluster to a trial arm. The intervention group will be offered the Smoke Free Homes package (*Smoke Free Homes: a resource for Muslim religious teachers*), trained in its use, and will subsequently implement the package in their religious settings. The remaining clusters will not be offered the package until the completion of the study and will form the control group. At each cluster, we aim to recruit around 50 households with at least one adult resident who smokes tobacco and at least one child or a non-smoking adult. Households will complete a household survey and a non-smoking individual will provide a saliva sample which will be tested for cotinine. All participant outcomes will be measured before and after the intervention period in both arms of the trial. In addition, a purposive sample of participants and religious leaders/teachers will take part in interviews and focus groups.

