## Background

Every year an estimated 79,000 adults die due to exposure to second-hand smoke (SHS) from tobacco in European Union countries
[1], of which more than 11,000 are from the United Kingdom (UK)
[2]. It has been more than six years since the legislation to ban smoking in enclosed public places was implemented in the UK. This has resulted in a welcome decline in SHS exposure and also illustrates the positive role of comprehensive smoke-free legislation. However, it is concerning that certain population subgroups (that is, lower socioeconomic status and certain ethnic groups) with the greatest SHS exposure benefited the least from the change
[3]. As expected, living in a home without any smoking restrictions is an important determinant of exposure
[4,5]. SHS is associated with development of lung cancer, coronary heart disease, respiratory disease and stroke among adult non-smokers
[6-8]. Among children it also increases risk of other lower respiratory illnesses, chronic middle ear disease and sudden infant death syndrome
[1,9].

In the UK, an estimated 40% of Bangladeshi and 29% of Pakistani men regularly smoke cigarettes compared to the national average of 24% (these figures are from 2004 but are the latest available broken down by ethinicity)
[10]. Regular smoking has also been shown to be common (39%) among 14 to 15 year old boys of Bangladeshi-origin in a London-based survey
[10]. SHS is also common in Bangladeshi and Pakistani households. For example, a study in 2008 in a locality in which nearly 50% of the population was of South Asian origin, found that smoking takes place regularly in front of children in 42% (95% confidence interval: 35% to 50%) of all households with at least one smoker
[11]. Another study reported higher salivary cotinine among Bangladeshi-origin children in households with smokers compared to children from other ethnic backgrounds
[12]. Smoking quit rates are lower than the UK average in these groups despite a high motivation to quit
[13]. This may in part be due to a feeling of ‘isolation and marginalisation’ from the existing smoking cessation services and lack of benefit from smoke-free initiatives
[14].

Higher susceptibility and earlier onset of cardiovascular diseases (CVD)

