## Methods/design

### Study design

The design of this trial follows Phase II of the Medical Research Council’s (MRC) framework for the evaluation of complex interventions
[32]. This is a pilot cluster randomised control trial (CRCT) of ‘SFH’ in Islamic religious settings with an integrated qualitative study and preliminary health economic component. The pilot trial will be carried out in approximately 14 Islamic religious settings (for example, mosques with dependent Madrassas and men’s/women’s circles, Islamic schools for children and Islamic forums) which host communal prayers, and/or convene study circles for women and/or have regular Qur’an classes for children. The clusters will be randomised to the intervention and control group in a 1:1 ratio. Clusters allocated to the intervention arm will be offered the SFH package (*Smoke Free Homes: a resource for Muslim religious teachers*) and trained to implement the package in their settings. The clusters in the control arm will not be offered the package until the completion of the study. From each cluster, we aim to recruit approximately 50 households with at least one adult resident who smokes tobacco and at least one child or a non-smoking adult resident. Households will complete a household survey and a non-smoking individual will provide a salvia sample which will be tested for cotinine. All participant outcomes will be measured before and after the intervention period in both arms of the trial. In addition a purposive sample of participants and religious leaders/teachers will take part in interviews and focus groups. Figure 
1 shows the trial design and flow of participants through the trial.

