#### Inclusion criteria

Participating households must have:

1. An adult resident who smokes cigarettes or other form of tobacco on a regular basis.

2. A child (1- to 16-years old) or a non-smoking adult resident.

3. At least one resident who attends a participating cluster at least once a week (for example, a male adult who attends a mosque or a female adult who attends a women’s circle or a child who attends Qur’an classes).

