#### Exclusion criteria

1. Any household where all adult residents smoke cigarettes or other forms of tobacco on a regular basis, and where there is no child resident.

2. There are no residents in the household who smoke on a regular basis.

3. Household members are regularly attending more than one cluster that is in the trial.

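### The household eligibility and saliva-collection rules put no non-smoking condition on a child donor, contradicting the sections that require a non-smoking donor and define the outcome in non-smokers

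*Protocol article*

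**What the plan says.** Three places attach the non-smoking condition to adults only:

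- Participant eligibility (households), Inclusion criteria, item 2: a household needs "A child (1- to 16-years old) or a non-smoking adult resident".
- Exclusion criteria for households, item 1: a household in which every adult smokes is removed only if it also meets the condition "and where there is no child resident". The child's own smoking is not mentioned.
- Data Collection, Saliva: the sample is taken "at baseline from a child in the house or, in the absence of a child, from a non-smoking adult member of the household". An adult is the substitute only when there is no child.

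Four places require a non-smoker:

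- Abstract, Methods/Design: "a non-smoking individual will provide a saliva sample which will be tested for cotinine".
- Study design: "Households will complete a household survey and a non-smoking individual will provide a salvia sample".
- Participant screening and informed consent, for households with a child: "A non-smoking resident (ideally a child) will be asked to consent to provide a baseline".
- Definitive trial primary outcome: "salivary cotinine levels in non-smokers in the households at follow up".

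The Saliva section also notes that age-specific cotinine thresholds separating active from passive smoking exist. It does not say that they will be applied to the donors. Families who test positive for second-hand smoke (SHS) exposure at baseline are followed up at 90%, and those who test negative at 10%.

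**The concern.** Cotinine measures nicotine intake from any source. It measures SHS exposure only if the donor does not smoke. A recruitment officer who follows the Saliva section literally goes to the child first, whatever the child's smoking status. One who follows the consent section looks for a non-smoker and prefers a child.

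The age range runs to 16, and the Background itself states: "Regular smoking has also been shown to be common (39%) among 14 to 15 year old boys of Bangladeshi-origin". A smoking teenager in a recruited household is therefore a foreseeable case.

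The pilot exists largely to supply an effect size, an SD and an ICC for salivary cotinine (Research questions 3 and 4; Sample size; Pilot trial outcomes 8 and 9). A few active smokers among the donors could dominate all three, and the distorted values would then set the size of the definitive trial.

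**Working it through.** **Reading the rules together.** Two kinds of household expose the conflict.

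1. One smoking teenager as the only child, one smoking adult, one non-smoking adult. The Saliva section selects the teenager, because a child is present. The consent section rules the teenager out and points to the non-smoking adult.
2. All adults smoke and the only child is a smoking teenager. The inclusion criterion is met through the child, and exclusion 1 does not apply because there is a child. No resident is a permitted donor under the consent section.

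**Inputs for scale.** The article gives no sample size to reproduce. From its Sample size and Saliva sections: 14 clusters, 7 per arm; 50 households per cluster, of which 20 are expected to be positive; follow-up of 90% and 10%; attrition of 20%; SD 1.38; difference 0.20 ng/mL; reduction 28%. Cotinine in smokers and the share of donors who smoke are not given and are assumed below.

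**Analysed per arm.** Positives: 7 × 20 = 140. Negatives: 7 × 30 = 210. Followed up: 140 × 0.9 + 210 × 0.1 = 147. After 20% attrition: 147 × 0.8 = 117.6, about 118.

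**Implied mean.** If the 0.20 difference and the 28% reduction are the same effect, 0.20 / 0.28 = 0.71 ng/mL.

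**Shift in the raw arm mean from one smoking donor**, (smoker value − 0.71) / 118:

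| Assumed smoker cotinine (ng/mL) | Shift (ng/mL) |
|---|---|
| 15 | 0.12 |
| 30 | 0.25 |
| 100 | 0.84 |

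One donor equals the 0.20 difference at 0.20 × 118 + 0.71 = 24.3 ng/mL. Below that it takes more than one; at 15 ng/mL, two donors give 0.24.

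**SD with a share p of smokers.** The variance is (1 − p) × 1.38² + p × S² + p(1 − p)(M − 0.71)², where M and S are the smokers' assumed mean and SD.

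- M = 100, S = 0: SD about 10.0 at p = 1% and 14.0 at p = 2%.
- M = 15, S = 10: SD about 2.2 at p = 1% and 2.8 at p = 2%.

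For illustration, take a raw-scale comparison with two-sided alpha 0.05, 80% power and no design effect. SD 1.38 and difference 0.20 need 748 per arm. In the mildest 2% case, with SD 2.8 and the difference diluted to 0.20 × 0.98, the figure is 3,215.

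**Is a share of 1 to 2% plausible?** If child donors were spread evenly over ages 1 to 16 and both sexes, with 39% smoking among boys aged 14 to 15 and none elsewhere, the share would be 2/16 × 0.5 × 0.39 = 2.4%. This is an illustration, not an estimate for the trial.

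**Effect of follow-up sampling.** The overall follow-up fraction is 0.4 × 0.9 + 0.6 × 0.1 = 0.42. If smokers were classed as SHS-positive, their share among those followed up would rise by 0.9 / 0.42 = 2.1-fold.

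**The case against.** A reader might infer that the plan as a whole admits smoking teenagers and counts them as SHS-positive. The documents do not support that. The consent section is itself a saliva rule; it requires a non-smoking donor, and it already allows another resident to give the sample when the child smokes. Consent comes before any baseline assessment, and the outcome is defined in non-smokers. This objection stands: the defect is a contradiction between sections, not a uniform rule that lets smokers in.

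The absence of a numerical upper cut-off is weak evidence. An article may leave it to the full protocol or the analysis plan, and the Saliva section shows that the authors know of such thresholds.

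The sizes rest on assumed smoker cotinine, an assumed share of smokers and analysis on the raw scale, which the article does not fix. It would be wrong to say that one smoker always outweighs the target difference; below about 24 ng/mL that fails. The 39% covers one sex, two years of age and one ethnic group in London, whereas the trial recruits both sexes in Birmingham and West Yorkshire. All of this stands.

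It is also true that baseline sampling precedes randomisation, so a smoking donor adds noise and chance imbalance and does not systematically favour an arm. That this is a pilot without a power claim is a weaker defence, because the SD, ICC and effect size are its products. A log transformation might reduce the leverage of high values, but it would not make the donor a non-smoker.

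**Conclusion.** The concern holds as an internal contradiction about who gives the primary-outcome sample. The household inclusion and exclusion criteria and the Saliva section cannot be reconciled as written with the abstract, Study design, the consent section and the primary outcome definition. Followed literally, the Saliva section can put an active smoker into an outcome meant for non-smokers, and the eligibility criteria can admit a household with no valid donor.

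That conclusion needs no arithmetic. The size of the damage does, and it is conditional: about 0.12 to 0.84 ng/mL per smoking donor in the raw arm mean for assumed values of 15 to 100 ng/mL, with about 118 analysed per arm and an implied mean of 0.71. The SD would at least rise noticeably at a 1 to 2% share of smokers. How many smoking donors there would be cannot be read from the documents.

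**What to change.** - In household inclusion criterion 2 and in the Saliva section, name the donor as a non-smoking child or a non-smoking adult. Replace the condition that no child is present with one that no non-smoking child is available, so that another non-smoking resident is used when the child smokes.
- Align household exclusion 1 so that every household has at least one non-smoking potential donor.
- State that the age-specific active-smoking threshold already referred to in the Saliva section is applied to the baseline sample, so that donors above it are neither classed as SHS-positive nor included in the SHS outcome. If the full protocol or analysis plan already holds this rule, refer to it. That sample is taken before randomisation, so the exclusion cannot depend on allocation.
- Keep high follow-up values in the main analysis and add a sensitivity analysis without them. Removing them from the main analysis would select on a post-randomisation value, and the Aim section lists smoking uptake among the things the intervention may change. Donors who start smoking during follow-up will therefore remain in the main estimate.

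The cost is a wording change in three places and a cut-off applied to an assay that is already planned. A few households will be lost or will change donor.

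### Saliva donors need only be non-smokers, so cotinine from a donor's own smokeless tobacco or nicotine replacement would be read as second-hand smoke exposure and could inflate the SD the pilot is meant to supply

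*Protocol article*

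**What the plan says.** Every rule on who may give saliva is written in terms of smoking:

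- Household inclusion criteria: "A child (1- to 16-years old) or a non-smoking adult resident".
- Participant screening and informed consent, households with a child: "A non-smoking resident (ideally a child) will be asked to consent to provide a baseline" saliva sample. The child is preferred but not required. The second category is "Households with adult residents only and at least one non-smoking adult living with a smoker", where the non-smoking adult is the donor.
- Saliva: the sample comes "from a child in the house or, in the absence of a child, from a non-smoking adult member of the household".
- Household exclusion criteria: "Any household where all adult residents smoke cigarettes or other forms of tobacco on a regular basis", where there is also no child. Other forms of tobacco are here the object of the verb smoke, so chewed tobacco falls outside.

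On the assay, the Saliva section states: "Cotinine is a metabolite of nicotine that can be measured in three main forms: serum, saliva and urine". It adds that "salivary cotinine is the most sensitive and specific measure of exposure to tobacco". It then treats a positive baseline test as SHS exposure and uses it to set follow-up sampling: 90% of positive families and 10% of negative ones. It mentions published thresholds for active and passive smoking but adopts no cut-off and gives no rule for high samples.

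The definitive trial's primary outcome would be "salivary cotinine levels in non-smokers in the households at follow up".

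**The concern.** By the article's own description, cotinine reflects nicotine from any source. Reading a positive as SHS exposure is sound only if the donor takes in no nicotine directly, and the donor rules do not secure this. Followed as written, they admit a never-smoker who chews tobacco or a former smoker on nicotine replacement.

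A smoke-free home cannot lower cotinine that comes from the donor's own use. Such a donor would be labelled SHS-positive, would very likely be selected for follow-up, and would contribute a value that may lie far outside the range of passive exposure. The pilot exists to supply the effect size, SD and ICC for the definitive trial. A few such values could spoil the SD in particular, and the same outcome definition would carry forward.

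**Working it through.** **Inputs from the article.** Seven clusters per arm (Randomisation). 50 households per cluster, at least 20 of them positive, attrition at most 20%, difference 0.20 ng/mL, 28% reduction, SD 1.38 (Sample size). Follow-up of 90% of positives and 10% of negatives (Saliva). No sample size, alpha or power is stated, so there is no planned figure to reproduce.

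**Assumptions.** A user's cotinine, C, and the share of users, p, are not in the article, so ranges are shown. The SD of 1.38 is taken to be in ng/mL. Alpha 0.05 two-sided and 80% power are assumed for context only.

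**1. Followed donors per arm.** 7 × (0.9 × 20 + 0.1 × 30) × 0.8 = 7 × 21 × 0.8 = 117.6.

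**2. Influence of one donor on an arm mean.** The excess that moves the mean by 0.20 is 0.20 × 117.6 = 23.5 ng/mL. Assumed excesses of 20, 100 and 200 ng/mL give shifts of 20/117.6 = 0.17, 100/117.6 = 0.85 and 200/117.6 = 1.70 ng/mL.

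**3. Effect on the SD, with no imbalance between arms.** The implied control mean is 0.20/0.28 = 0.714 ng/mL. With a share p of donors at C and the rest at mean 0.714 and SD 1.38:

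variance = (1 − p) × 1.38² + p(1 − p)(C − 0.714)²

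For p = 1% and C = 20: 0.99 × 1.904 + 0.0099 × 19.286² = 1.885 + 3.682 = 5.57, so the SD is 2.36.

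The number per arm before clustering is 2 × (1.960 + 0.842)² × variance / 0.20².

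| p | C (ng/mL) | SD | n per arm |
|---|---|---|---|
| 0 | – | 1.38 | 748 |
| 1% | 10 | 1.65 | 1,075 |
| 0.5% | 20 | 1.94 | 1,470 |
| 1% | 20 | 2.36 | 2,185 |
| 2% | 20 | 3.03 | 3,594 |
| 1% | 100 | 9.97 | 39,040 |

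In the pilot, 1% of 117.6 is about one donor per arm.

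**4. Enrichment by the sampling rule.** If users are among the positives, each is followed with probability 0.9 × 0.8 = 0.72. If 2% of the 350 recruited per arm were users, 7 × 0.72 = 5.0 would be followed, or 5.0/117.6 = 4.3%. The sampling roughly doubles their share.

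**5. How common use must be among adult donors.** Suppose only adults are users. A 1% share of all donors then needs 5% of adult donors to be users if adults are 20% of donors, or 10% if adults are 10%. The adult share is not stated.

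**6. ICC.** The direction is open. Users spread evenly add variance within clusters and lower the ICC; users concentrated in a few clusters could raise it. The article gives nothing from which to size this.

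**The case against.** The strongest reply is that nothing in the article shows such donors exist. Smokeless tobacco and nicotine replacement are not mentioned, and the prevalence and levels used above are assumptions. That stands: the size is conditional. The gap itself is not, because it lies in the stated donor rules.

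Children are the preferred donors, so most of the risk sits with adults. That stands too and limits the size. Adults are not confined to child-free households, however, since the consent section makes the child only the ideal donor and takes no sample from an unwilling one.

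A reader might infer that the 0.20 ng/mL difference will be swamped by bias. The article does not support that. Expected imbalance between randomised arms is zero; a shift needs chance imbalance, which is plausible with seven clusters per arm. The same person is sampled twice, so stable use would show at baseline. The 0.20 is also a planning figure for the definitive trial: at 748 per arm one donor would need an excess of 0.20 × 748 = 150 ng/mL. And the pilot's standard error for the difference is already 1.38 × √(2/117.6) = 0.18, a 95% half-width of 0.35 before clustering, so it could not resolve 0.20 in any case.

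A reader might also infer that users could never be identified afterwards. That goes too far. The Survey section lists broad dimensions, not items, and the questionnaire may record other tobacco use. A cotinine cut-off, if the full protocol or analysis plan applies one, would flag very high values whatever their source. Neither is tied to donor selection or to the SHS-positive label in the article.

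Last, the pilot is meant to test its assumptions, so odd values would be informative. They inform only if their cause is recorded.

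**Conclusion.** The point holds in a limited form. The donor rules and the reading of a positive test do not fit together: the assay is described as a measure of tobacco exposure, the donor is screened only for smoking, and the result is labelled SHS exposure. The most robust consequences are misclassification in the follow-up sampling and inflation of the SD, since neither needs imbalance between arms. A bias in the effect estimate is possible by chance only, and distortion of the ICC is possible but not quantified.

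The figures rest on assumed user levels and shares, on cotinine analysed on its raw scale, and on the article's own recruitment and attrition expectations. If use among adult donors is rare or their cotinine low, the effect is small. If about one followed donor per arm is a user at 20 ng/mL, the SD is overstated by about 70% (2.36/1.38 = 1.71). The sponsor should act because the remedy is cheap and recruitment was still open when the article was written.

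**What to change.** In Participant screening and informed consent, and in Saliva:

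- At each saliva collection, ask the donor (or parent) about recent use of smokeless tobacco and nicotine replacement.
- At baseline, if use is reported, take the sample from another eligible resident. Baseline precedes randomisation, so this cannot bias the arms.
- Base the SHS-positive classification, and hence the 90%/10% follow-up sampling, on donors without their own nicotine use.
- Keep donors who report use only at follow-up in the main intention-to-treat estimate. Report the effect size, SD and ICC without them as a sensitivity analysis. Dropping them from the main estimate would be an exclusion after randomisation, based on self-report that the intervention might itself influence, and would conflict with the intention-to-treat principle in Data analysis.

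The cost is one extra question per collection and a line in the donor rule, with no new visit or assay. A few households will need a different donor or will give no analysable sample.
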